# Additional hepatic ^166^Ho-radioembolization in patients with neuroendocrine tumours treated with ^177^Lu-DOTATATE; a single center, interventional, non-randomized, non-comparative, open label, phase II study (HEPAR PLUS trial)

**DOI:** 10.1186/s12876-018-0817-8

**Published:** 2018-06-15

**Keywords:** NET, Neuroendocrine tumour, Liver metastasis, Radioembolization, Holmium-166, PRRT, Lutetium-177, ^177^Lu-DOTATATE

## Abstract

**Background:**

Neuroendocrine tumours (NET) consist of a heterogeneous group of neoplasms with various organs of origin. At diagnosis 21% of the patients with a Grade 1 NET and 30% with a Grade 2 NET have distant metastases. Treatment with peptide receptor radionuclide therapy (PRRT) shows a high objective response rate and long median survival after treatment. However, complete remission is almost never achieved. The liver is the most commonly affected organ in metastatic disease and is the most incriminating factor for patient survival. Additional treatment of liver disease after PRRT may improve outcome in NET patients. Radioembolization is an established therapy for liver metastasis. To investigate this hypothesis, a phase 2 study was initiated to assess effectiveness and toxicity of holmium-166 radioembolization (^166^Ho-RE) after PRRT with lutetium-177 (^177^Lu)-DOTATATE.

**Methods:**

The HEPAR PLUS trial (“***H****olmium*
***E****mbolization*
***P****articles for*
***A****rterial*
***R****adiotherapy*
***P****lus*
^*177*^***Lu****-DOTATATE in*
***S****alvage NET patients”*) is a single centre, interventional, non-randomized, non-comparative, open label study. In this phase 2 study 30–48 patients with > 3 measurable liver metastases according to RECIST 1.1 will receive additional ^166^Ho-RE within 20 weeks after the 4th and last cycle of PRRT with 7.4 GBq ^177^Lu-DOTATATE. Primary objectives are to assess tumour response, complete and partial response according to RECIST 1.1, and toxicity, based on CTCAE v4.03, 3 months after ^166^Ho-RE. Secondary endpoints include biochemical response, quality of life, biodistribution and dosimetry.

**Discussion:**

This is the first prospective study to combine PRRT with ^177^Lu-DOTATATE and additional ^166^Ho-RE in metastatic NET. A radiation boost on intrahepatic disease using ^166^Ho-RE may lead to an improved response rate without significant additional side-effects.

**Trial registration:**

Clinicaltrials.gov NCT02067988, 13 February 2014. Protocol version: 6, 30 november 2016.

## Background

In accordance with the most recent WHO/ENETS criteria, grade 1 and 2 neuroendocrine tumours (G1-/G2NET) are regarded as well- to moderately-differentiated tumours and grade 3 NET (G3NET) as poorly-differentiated NET or neuroendocrine carcinomas (NEC) [1, 2]. At diagnosis, 21% of all G1NET, 30% of all G2NET and 50% of all G3NET have distant metastases, of which the liver is most commonly affected [3, 4]. A correlation between the organ of origin and the likelihood of metastasis exists. For example, rectal NET has a slim chance of distant metastasis (5%) compared with pancreatic or colonic NET (respectively 64% and 53–86%) [3, 5]. Considering these numbers, many patients will be ineligible for curative treatment, which currently only includes surgical resection of the primary tumour.

Most G1-/G2NET have membrane receptors for somatostatin, allowing for targeted therapies, of which somatostatin-analogs are the most commonly used (e.g. octreotide). Treatment with somatostatin-analogs, chemotherapeutics and kinase inhibitors show only limited objective response rates in G1-/G2NET [6–12]. In addition, systemic therapies give rise to systemic side effects. In the last decade, the treatment of G1-/G2NET with peptide receptor radionuclide therapies (PRRT) has increased. High objective imaging response rates (CR + PR 29–58%) [13–17], clinical and biological response rates and a long median survival (95–128 months after diagnosis, 46 months after treatment) [13, 14] can be achieved after PRRT (Fig. 1).

**Fig. 1 Fig1:**
[figure not shown]
Example of ^177^Lu-DOTATATE in NET. Upper row: planar whole body ^111^In-pentetreotide scintigraphy. Lower row: venous phased CT of the liver. On the left baseline imaging and on the right imaging after ^177^Lu-DOTATATE treatment

All studies include high percentages of patients with liver metastases and show a dismal prognosis with increasing liver involvement (Table 1). As surgical resection techniques develop, some forms of hepatic involvement can be treated surgically. However, as three different patterns of hepatic metastases are described in NET, patients with the most common ‘diffuse pattern’ are not eligible for surgical resection (Table 2) [4]. Besides, most systemic therapies have a limited objective response rate. This indicates a need for improved treatment of extensive liver disease. In accordance with the ENETS guideline published in 2012, the treatment of choice in patients with NET liver metastases with a ‘diffuse’ or unresectable ‘complex pattern’, consists of systemic treatment followed by liver directed treatment [4]. Hepatic radioembolization (RE) is one of the liver directed treatments and it is an established minimal invasive treatment of patients with liver malignancies. RE has been demonstrated to be effective and well tolerated in primary, as well as secondary liver malignancies. A recent meta-analysis by Devcic et al. showed an average objective response rate (CR + PR) of 50% and an average disease control rate of 86% in a heterogeneous group of NET treated with RE [18]. ^166^Ho-RE is quite similar to ^90^Y-RE, but its distinct advantages will be discussed later on. Figure 2 shows an example of ^166^Ho-RE in a NET patient.

**Table 1 Tab1:** Liver involvement as a poor prognostic factor in different therapeutic studies

Author	Treatment	N	Liver involvement	Median survival (months)	5-year survival	*p* values
Chamberlain (2000) [46]	Surgical resection	85	0–25%	–	90%	
			25–50%	–	83%	
			50–75%	47	80%	
			> 75%	24	–	
Yao (2001) [47]	Surgical resection	16	≤4 liver metastases	46	–	< 0.05
			> 4 liver metastases	20	–	
Gupta (2005) [48]	TAE or TACE	123	0–25%	86	–	
			25–50%	30	–	< 0.10
			50–75%	39	–	< 0.17
			> 75%	20	–	< 0.05
Kwekkeboom (2008) [14]	PRRT	310	None	> 48	–	
			Moderate	> 48	–	
			Extensive	25	–	< 0.01

Legend: *TAE* transarterial (bland) embolization, *TACE* transarterial chemoembolization, *PRRT* peptide receptor radionuclide therapy

**Table 2 Tab2:** NET Liver involvement patterns [4]

	Involvement	Incidence
Simple pattern	One lobe or two adjacent lobes	20–25%
Complex pattern	Primarily one lobe and smaller satellites contralaterally	10–15%
Diffuse pattern	Multifocal disease	60–70%

## Methods

### Study design

The HEPAR PLUS study is a single centre, interventional, non-randomized, non-comparative, open label study. In this phase 2 study all patients will receive additional ^166^Ho-RE after ^177^Lu-DOTATATE. Overall, 30–48 patients with metastasized NET will be investigated for efficacy and toxicity.

### Subjects

Patients with NET and liver metastasis, who completed 4 cycles of 7.4 GBq ^177^Lu-DOTATATE, will receive additional ^166^Ho-RE within 20 weeks of the last/fourth cycle of ^177^Lu-DOTATATE. At time of recruitment, all included patients have no need for conventional treatment options like surgery or chemotherapy. In the Netherlands, ^177^Lu-DOTATATE is often a first- or second-line treatment. Previous treatments prior to ^177^Lu-DOTATATE were no exclusion criterium. Detailed inclusion and exclusion criteria are listed in Table 3.

**Table 3 Tab3:** Inclusion and exclusion criteria

Inclusion criteria	Exclusion criteria
Patient must have given a written informed consent	Brain metastases or spinal cord compression, unless irradiated > 4 weeks prior to ^166^Ho-RE and stable for at least 1 week without steroids
≥ 18 years of age	Serum bilirubin > 1.5 x upper limit of normal
Confirmed histological diagnosis NET	Glomerular filtration rate < 35 ml/min
Prior treatment with 4 cycles of 7.4 GBq ^177^Lu-DOTATATE within 20 weeks before ^166^Ho-RE	Alkaline phosphatase, alanine aminotransferase or aspartate aminotransferase > 5 x upper limit of normal
Life expectancy > 12 weeks	Leucocytes < 2.0 × 10^9^/l and/or platelet count < 50 × 10^9^/l
WHO performance score 0–2	Significant cardiac event within 3 months of inclusion
≥ 3 measurable liver lesions according to RECIST 1.1	Patients suffering from diseases with an increased chance of liver toxicity
Negative pregnancy test for women of childbearing potential	Patients declared incompetent or suffering from psychic disorders making comprehensive judgment impossible
No nursing activities for women of childbearing potential	Severe bile duct abnormalities: papillotomy, cholecystectomy, biliary stents and bilidigestive anastomosis are allowed
Acceptable method of contraception	Body weight > 150 kg
	Severe contrast allergy
	Liver tumour involvement > 70% on CT

### Time schedule

Recruitment will take place between Augustus 2014 and January 2019. First participant was enrolled in November 2014.

### Medical device

^166^Ho-microspheres are produced by incorporating non-radioactive ^165^Ho and its acetylacetonate complex (^165^HoAcAc) in a poly(L-lactic acid) matrix to form microspheres with an average diameter of 30 μm. By neutron-activation in a nuclear facility, the prescribed amount of radioactive ^166^Ho-microspheres are produced [19, 20]. The radionuclide ^166^Ho has a half-life of 26.8 h, is a beta-emitter (Ε_βmax_ = 1.85 MeV) and a gamma emitter (Ε_γ_ = 81 keV). Due to their additional photon emitting properties, ^166^Ho-microspheres can be visualized and quantified using SPECT imaging [21, 22].

### Recruitment

All patients have previously been treated with four cycles of ^177^Lu-DOTATATE. After the fourth cycle patients are eligible for study inclusion. The study physician ([name]) and principal investigator ([name]) inform all patients; thereafter informed consent will be obtained. On the informed consent form, participants can indicate whether they wish to receive a summary of the trial results, once the trial is completed.

### Statistical analysis

This single arm open label study will have a sequential design. Stopping boundaries are determined such that an overall one-side alpha of at the most 0.05 is maintained in case the true tumour response is 20%. Early termination at a response interim analysis (after 30, 36 or 42 patients) is determined by pre-defined boundaries on the number of partial and complete responses according to RECIST 1.1 (Table 4). A superiority or futility boundary may be reached or crossed before 30 patients are reached, but the study will continue to at least 30 patients to allow estimation of the key secondary endpoints. The sequential design with boundaries as given in Table 4 will have a power of 90% to reach a positive tumour response decision in case the true target lesions tumour response is 40%. The exact overall one-sided type I error is 4.5%.

**Table 4 Tab4:** Stopping boundaries for early termination at interim analysis

Analysis	Sample Size	Lower boundary	Upper boundary
1	30	5	11
2	36	6	13
3	42	7	14
4	48	15	16

Interim analysis of toxicity with descriptive statistics (N, mean, median, etc.) will be performed for every 3 patients. All analysis will be performed in the Full Analysis Set (FAS), including all patients who received at least the scout dose procedure (see below). The Per Protocol Set (PPS) will include all patients who complied with the protocol up to at least 3 months. PPS analyses will be used for the primary endpoint. For the assessment of the primary objective at least 30 patients should have a 3 months follow-up CT-scan. If patients do not reach the 3 months follow-up CT-scan or receive a new treatment prior to the evaluation moment, a new patient will be included for the PPS analysis.

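### Table 4 continues past 42 patients with 8 or 9 responses, although the final success boundary of 16 of 48 is then out of reach

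*Protocol article*

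**What the plan says.** The Statistical analysis section describes a single-arm sequential design with response looks after 30, 36 and 42 patients and a final analysis at 48. Stopping rests on the number of complete and partial responses: "Early termination at a response interim analysis (after 30, 36 or 42 patients) is determined by pre-defined boundaries". Table 4, headed "Stopping boundaries for early termination at interim analysis", gives these values:

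| Analysis | Patients | Lower | Upper |
|---|---|---|---|
| 1 | 30 | 5 | 11 |
| 2 | 36 | 6 | 13 |
| 3 | 42 | 7 | 14 |
| 4 | 48 | 15 | 16 |

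The boundaries are set so that an "overall one-side alpha of at the most 0.05 is maintained in case the true tumour response is 20"%, with a "power of 90% to reach a positive tumour response decision in case the true target lesions tumour response is 40"%. The section adds: "The exact overall one-sided type I error is 4.5"%.

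How a boundary acts is shown by the sentence "A superiority or futility boundary may be reached or crossed before 30 patients are reached": reaching it is enough. Patients without an evaluable 3-month scan are replaced ("a new patient will be included for the PPS analysis"), so the evaluable numbers at each look stay as tabulated. The section gives one reason for going on after a boundary has been met, namely estimation of key secondary endpoints, and attaches it only to the minimum of 30 patients.

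**The concern.** A futility boundary should at least catch every count from which success is no longer possible. Rows 3 and 4 of Table 4 do not fit together in this respect. Row 3 tells the trial to continue with 8 to 13 responses at 42 patients. Row 4 requires 16 at 48, and only six patients come in between. From 8 or 9 responses the gap cannot be closed, whatever the true response rate.

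At stake is patient exposure, not the validity of the result. Up to six more patients would go through angiography, a scout dose and radioembolization after the tumour-response question has been settled. The situation is most frequent when the true rate is low, which is where a futility rule is meant to work.

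**Working it through.** **Inputs.** All come from the Statistical analysis section and Table 4: looks at n = 30, 36, 42, 48; lower boundaries 5, 6, 7, 15; upper boundaries 11, 13, 14, 16; null rate 20%; alternative 40%.

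**Step 1: reproduce the stated error rates.** Let S be the cumulative number of responses. Between looks, m new patients add a Binomial(m, p) count, with m = 30, 6, 6, 6. At each look the probability mass with S ≥ upper is counted as success and the mass with S ≤ lower as futility. The rest is carried forward.

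Probability of a positive decision by look:

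| True rate | n = 30 | n = 36 | n = 42 | n = 48 | Total |
|---|---|---|---|---|---|
| 20% | 0.0256 | 0.0048 | 0.0113 | 0.0035 | 0.0452 |
| 40% | 0.7085 | 0.0694 | 0.0899 | 0.0301 | 0.8979 |

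These match the stated 4.5% and 90%. If the upper boundary had to be exceeded rather than reached, the totals would be 0.0197 and 0.827, which do not match. The inclusive reading of the upper boundary is therefore secure. The lower boundary hardly moves these figures, so its inclusive reading rests on the sentence about a boundary being reached or crossed. If it were strict, 7 of 42 would also continue without any chance of success, and the inconsistency would be larger.

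**Step 2: what can still be reached from 42 patients.** Maximum final count = S + 6; success needs S + 6 ≥ 16, that is S ≥ 10.

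| Responses at 42 | Maximum at 48 | Chance of 16 or more if p = 40% |
|---|---|---|
| 8 | 14 | 0 |
| 9 | 15 | 0 |
| 10 | 16 | 0.4⁶ = 0.0041 |

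The earlier looks do not have this fault. The lowest continuing count is 6 of 30 (maximum 6 + 18 = 24) or 7 of 36 (maximum 7 + 12 = 19), both above 16.

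**Step 3: how often it happens.** Probability of leaving look 3 with 8 or 9 responses and continuing:

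| True rate | 8 of 42 | 9 of 42 | Sum |
|---|---|---|---|
| 20% | 0.0786 | 0.1096 | 18.8% |
| 25% | 0.0522 | 0.0970 | 14.9% |
| 30% | 0.0215 | 0.0514 | 7.3% |
| 40% | 0.0011 | 0.0042 | 0.5% |

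At 20% the total probability of continuing past look 3 is 0.455, so 0.188/0.455 = 41% of the trials that go on to 48 do so with no chance of success.

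**Step 4: raise the look-3 lower boundary to 9.** No path that this removes could have ended in success, so the success probability cannot change. The recursion confirms it:

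| True rate | P(positive), lower 7 | P(positive), lower 9 | Expected N, lower 7 | Expected N, lower 9 |
|---|---|---|---|---|
| 20% | 0.0452 | 0.0452 | 38.98 | 37.85 |
| 30% | 0.4484 | 0.4484 | 40.47 | 40.03 |
| 40% | 0.8979 | 0.8979 | 33.77 | 33.73 |

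The saving is 6 × the probability from step 3, for example 6 × 0.188 = 1.13 patients at 20%. These expected sizes assume that enrolment stops as soon as a boundary is met.

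**The case against.** The strongest reply is that nothing the trial will report becomes wrong. A trial with 8 or 9 responses at 42 patients still ends, correctly, as not positive, and the printed type I error and power are true as they stand. The average saving is about one patient at a true rate of 20% and 0.04 at 40%. All of this stands, and it keeps the severity modest.

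Three further points limit what may be claimed.

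- **The extra patients are not without use.** A reader might infer that patients 43 to 48 contribute nothing. The Primary objectives section makes the safety and toxicity profile a primary objective alongside response, and the Monitoring section schedules a safety analysis after patient 48. Only the response decision is fixed. The protocol does not, however, offer toxicity data as its reason for continuing past 42, so the inconsistency remains.
- **Thirty patients are a floor.** A reader might take the sentence on secondary endpoints to mean that 30 are sufficient. It sets a minimum and does not say that more are unneeded.
- **Six is an upper limit.** Response is read at 3 months and no pause in enrolment is described. The Time schedule section puts the first enrolment in November 2014 and the end of recruitment in January 2019, about 50 months. If 48 patients accrued evenly (an assumption), that is about one a month. Some three of the last six could then have been treated before the 42nd patient's scan is read.

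It is also tempting to call the other lower boundaries too lenient. From 7 of 36 or 10 of 42 the chance of success is small but not zero. How readily to stop there is a trade-off against power, which is the sponsor's to make, and not an error.

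**Conclusion.** The inconsistency holds. Row 3 of Table 4 lets the trial continue from two counts, 8 and 9 of 42, from which row 4 cannot be satisfied, and no other part of the article supplies a stopping rule or a reason for going on in that case. The probability is 18.8% at a true rate of 20% and falls to 0.5% at 40%. The consequence is up to six further patients treated after the response decision is settled.

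Severity is modest, because the stated alpha, power and conclusions are unaffected. The impossibility itself follows by subtraction and needs no assumption about the response rate. The probabilities assume independent patients with a common response rate, inclusive boundaries that are followed, and the evaluable numbers of Table 4 at each look.

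**What to change.** In Table 4, change the lower boundary at analysis 3 from 7 to 9. Type I error (4.52%) and power (89.79%) stay exactly the same, so no other figure in the section needs revision. The cost is fewer patients for toxicity and secondary estimates in trials that now stop at 42. If the sponsor wants those patients for the toxicity objective, the alternative is to keep 7 and state that reason for continuing at 8 or 9 responses.

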#### Angiography

Patients are admitted for 3 days (2 nights) starting the day prior to the angiography. After physical examination and relevant laboratory testing, patients are pre-hydrated to prevent kidney damage, and started on proton pump inhibitors for 6 weeks (pantoprazole once a day 40 mg). Premedication 1 h prior to the angiography consists of one dose of corticosteroids, antihistamines and anti-emetics (respectively dexamethasone 10 mg, clemastine 1 mg and ondansetron 8 mg), at the same time a tranquilizer is offered to the patient (oxazepam 10 mg). If the patient is familiar with a mild to moderate contrast allergy, additional corticosteroids and antihistamines will be given prior to the angiography according with national guidelines of the Central Accompaniment Institution (CBO in Dutch) [24].

A skilled and trained interventional radiologist will perform all angiographies of the upper abdominal vessels. A catheter is introduced via one of the femoral arteries by the Seldinger technique. After identifying all arteries supplying the liver, additional branches of these arteries that supply other organs than the liver are coiled, if needed. This usually involves the gastroduodenal artery (GDA) and right gastric artery (RGA).

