#### Scout dose

Once successful identification of the supplying arteries and occlusion of additional branches has been performed, a scout dose of 250 MBq ^166^Ho-microspheres will be administered [20, 25]. Due to the photon emission of ^166^Ho, distribution of the microspheres, lung shunting and extrahepatic depositions can all be assessed using SPECT/CT. Planar imaging and SPECT/CT will be performed following the angiography and evaluated qualitatively as well as quantitatively. Extrahepatic deposition of activity is a contra-indication for treatment. Lung shunting will be assessed by planar imaging and SPECT/CT and should not exceed the maximum tolerable lung absorbed dose (i.e. 30 Gy).

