#### Treatment

If the pre-treatment assessment is successful, patients return to the angiography suite for the treatment angiography combined with the ^166^Ho-RE. This will take place on the same day as the pre-treatment angiography and scout dose procedure (see Fig. 3). Based on the results of the dose escalation study (i.e. HEPAR I trial), a whole liver absorbed dose of 60 Gy was determined to be safe. A whole liver absorbed dose of 60 Gy leads to the following equation for activity calculation:$$ {A}_{{}^{166} Ho}(MBq)=3781\ \left( MBq\ast \frac{Gy}{J}\right)\ast liver\ weight\ (kg) $$

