##### Primary objectives

Two distinct objectives are the focus of our study. Tumour response on CT at 3 months of follow-up will be the first primary objective. This is defined as complete response (CR = disappearance of all lesions) or partial response (PR = ≥30% decrease in the sum of the longest diameters of the target lesions, compared to baseline measurements). The second primary objective is to establish the safety and toxicity profile of treatment with ^166^Ho-RE as an additional treatment after ^177^Lu-DOTATATE, using the Common Terminology Criteria for Adverse Events (CTCAE version 4.03) [26].

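### The Full Analysis Set starts at the scout dose, so patients whose study angiography is abandoned before it are missing from the primary safety summary

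*Protocol article*

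**What the plan says.** The Statistical analysis section names two analysis sets. The FAS is used for all analysis and is defined as "including all patients who received at least the scout dose procedure". The Per Protocol Set takes patients who complied with the protocol to at least 3 months and is used for the primary endpoint. The article defines no separate safety set.

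Under Primary objectives, safety has primary status: "The second primary objective is to establish the safety and toxicity profile of treatment with" holmium radioembolization given after lutetium PRRT, graded by CTCAE.

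The order of events comes from the Treatment sections. Consent and screening precede the first angiography. At angiography, "A catheter is introduced via one of the femoral arteries by the Seldinger technique", and "additional branches of these arteries that supply other organs than the liver are coiled, if needed". The Scout dose section then makes the scout dose depend on that work: "Once successful identification of the supplying arteries and occlusion of additional branches has been performed, a scout dose of 250 MBq". The Treatment subsection places the treatment angiography "on the same day as the pre-treatment angiography and scout dose procedure", which names the angiography and the scout dose procedure as two items.

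The Monitoring section separately sends severe adverse (device) events to the Ethics Committee and the IDMC within 8 days, and a summary of them to the health inspectorate every 3 months. Neither duty is limited to the FAS.

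**The concern.** The study procedure begins before the point at which a patient enters the FAS. Admission, contrast, femoral access and coiling all happen after consent, in order to deliver the study treatment. If the procedure is abandoned in that window, the patient is in no analysis set.

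Entry to the set can therefore depend on the outcome being measured. A complication severe enough to stop the procedure before the scout dose removes its own patient from both the numerator and the denominator of the safety summary. The share of patients in whom the procedure could not be completed also goes unreported in that summary. In a study of 30 to 48 patients, one event is 3.3 (1/30) to 2.1 (1/48) percentage points, so even one or two such patients can change how the safety profile reads.

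**Working it through.** **The plan's own figures.** The only figures that can be reproduced here are those of the sequential response design. An exact binomial recursion over the four looks (30, 36, 42, 48) was run, stopping for success at or above the upper boundary (11, 13, 14, 16) and for futility at or below the lower one (5, 6, 7, 15):

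- Response 20%: 0.0256 + 0.0048 + 0.0113 + 0.0035 = 0.0452, against a stated type I error of 4.5%.
- Response 40%: 0.7085 + 0.0694 + 0.0899 + 0.0301 = 0.898, against a stated power of 90%.

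Both agree. They concern tumour response only and do not depend on where a safety set starts.

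**Who is in which set.** Following a consented patient through the sections quoted above:

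| Course | FAS | Per Protocol Set |
|---|---|---|
| Angiography started, abandoned before scout dose | no | no |
| Complication before scout dose, scout dose still given | yes | only if compliant to 3 months |
| Scout dose given, no treatment dose | yes | not as a treated, compliant patient |
| Scout and treatment dose given | yes | if compliant to 3 months |

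Only the first row is lost to the analysed safety result.

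**How many patients that could be.** The article gives no abandonment rate, so f = 2%, 5% and 10% are assumptions. If N patients reach the scout dose, the expected number attempted but abandoned is N × f / (1 − f), and the chance of at least one is 1 − (1 − f)^N.

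| f (assumed) | N = 30: expected | N = 30: chance of at least one | N = 48: expected | N = 48: chance of at least one |
|---|---|---|---|---|
| 2% | 30 × 0.02/0.98 = 0.6 | 0.455 | 1.0 | 0.621 |
| 5% | 30 × 0.05/0.95 = 1.6 | 0.785 | 2.5 | 0.915 |
| 10% | 30 × 0.10/0.90 = 3.3 | 0.958 | 5.3 | 0.994 |

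These count abandoned procedures. They do not count complications, and a procedure may be abandoned without harm, for example because the vessels are unsuitable.

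**What it could do to a rate.** Suppose two patients are abandoned and, as the extreme case, both had a complication. Then 0/30 (0%) in the FAS becomes 2/32 (6.3%) among attempted procedures, and 3/30 (10.0%) becomes 5/32 (15.6%). If neither had a complication, 3/30 becomes 3/32 (9.4%), so the effect can also run slightly the other way.

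**The case against.** Four points can fairly be made for the plan.

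1. *Convention.* Starting a set at first exposure to the device is common. It matches an objective worded as the safety of treatment with holmium radioembolization, and it is wider than a treated-only set because it keeps scout-only patients. This stands as a reason to keep the FAS. It does not justify making it the only set for a primary safety objective, because catheterisation and coiling are part of delivering the treatment.

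2. *Wording.* The definition says scout dose procedure and not just scout dose, which might be stretched to cover the preparatory angiography on the same day. The narrower reading is the more natural one, because the Treatment subsection lists the two side by side and the Scout dose section makes one follow success in the other. If the wider meaning is intended, the definition should say so.

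3. *Oversight.* A reader might infer that complications before the scout dose go unseen. The Monitoring section does not support that, since severe events are reported whatever the analysis set. A reader might also infer that every patient with such a complication drops out, but those who still receive the scout dose remain in the FAS.

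4. *Size.* It is tempting to set one event in 30 against the figure of below 1% for more serious events in the Safety profile section. The events named there, REILD and inadvertent extrahepatic distribution of activity, require microspheres to have been given. They cannot occur before the scout dose, so that figure is no benchmark. The chances of at least one abandoned patient must likewise not be read as chances of a missed adverse event.

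A condensed article may also leave patient accounting to the full protocol or SAP. The point here rests on the stated rule that all analysis uses the FAS, and not on anything left out.

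**Conclusion.** The point holds in a limited form. As written, patients whose study angiography is started but abandoned before the scout dose fall outside both analysis sets, and the primary safety summary is conditional on technical success. The direction is towards a more favourable procedural safety rate to the extent that abandonment is caused by complications.

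The size cannot be computed from the article. At an assumed abandonment of 2% to 10%, about 0.6 to 3.3 patients per 30 in the FAS (1.0 to 5.3 per 48) lie outside the denominator, and an unknown share of them would have had a complication. The conclusion rests on reading the scout dose procedure as distinct from the angiography before it, and on no separate safety set being defined in the full protocol or SAP, which are not shown. It is a modest weakness that is cheap to remedy.

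**What to change.** In the Statistical analysis section, add a safety set of all consented patients in whom the study angiography was started, meaning that arterial access was obtained. In that set, report procedure-related adverse events and the number who did not proceed to the scout dose or to treatment, with reasons. Present this beside the toxicity in the FAS and in treated patients, without merging the two, so that device toxicity and procedural risk can each be read. Limit the statement that all analysis uses the FAS accordingly.

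The cost is a sentence or two in the analysis-set definition and one extra table. These patients are already consented and admitted, so no extra patients or visits are needed to record procedural events and reasons for stopping. The reported procedural complication rate may turn out slightly less favourable.
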